## Abstract

**Background:**

Hot flashes are a highly prevalent problem associated with menopause and breast cancer treatments. The recent findings from the Women's Health Initiative have important implications for the significance of a non-hormonal, mind-body intervention for hot flashes in breast cancer survivors. Women who take hormone therapy long-term may have a 1.2 to 2.0 fold increased risk of developing breast cancer. In addition, it is now known that hormone therapy with estrogen and progestin is associated with increased risk of cardiovascular disease and stroke. Currently there are limited options to hormone replacement therapy as non-hormonal pharmacological agents are associated with only modest activity and many adverse side effects. Because of this there is a need for more alternative, non-hormonal therapies. Hypnosis is a mind-body intervention that has been shown to reduce self-reported hot flashes by up to 68% among breast cancer survivors, however, the use of hypnosis for hot flashes among post-menopausal women has not been adequately explored and the efficacy of hypnosis in reducing physiologically measured hot flashes has not yet been determined.

**Methods/design:**

A sample of 180 post-menopausal women will be randomly assigned to either a 5-session Hypnosis Intervention or 5-session structured-attention control with 12 week follow-up. The present study will compare hypnosis to a structured-attention control in reducing hot flashes (perceived and physiologically monitored) in post-menopausal women in a randomized clinical trial. Outcomes will be hot flashes (self-report daily diaries; physiological monitoring; Hot Flash Related Daily Interference Scale), anxiety (State-Trait Anxiety Inventory; Hospital Anxiety and Depression Scale (HADS); anxiety visual analog scale (VAS rating); depression (Center for Epidemiologic Studies Depression Scale), sexual functioning (Sexual Activity Questionnaire), sleep quality (Pittsburgh Sleep Quality Index) and cortisol.

**Discussion:**

This study will be the first full scale test of hypnosis for hot flashes; one of the first studies to examine both perceived impact and physiologically measured impact of a mind-body intervention for hot flashes using state-of-the-art 24 hour ambulatory physiological monitoring; the first study to examine the effect of hypnosis for hot flashes on cortisol; and the first investigation of the role of cognitive expectancies in treatment of hot flashes in comparison to a Structured-Attention Control.

**Trial Registration:**

This clinical trial has been registered with ClinicalTrials.gov, a service of the U.S. National Institutes of Health, ClinicalTrials.gov Identifier: NCT01293695.

## Background

Hot flashes are the most common complaint of post-menopausal women [1,2]. Almost two-thirds of post-menopausal women have hot flashes and nearly 20% find them to be nearly intolerable [3]. It is estimated that over 25 million women in the United States may have hot flashes and 4 million may have severe hot flashes [4]. The experience of hot flashes can be very uncomfortable and can have a very negative impact upon the individual's quality of life [5] energy and sleep [6]. It was also reported that one-third of women with hot flashes described embarrassment and 20% described a general sense of a loss of control [7]. In addition, hot flashes are associated with decreased libido [4]. Hot flashes can significantly decrease quality of life, alter daily activities, and negatively affect sleep [2,8,9] in breast cancer survivors.

The standard of care for ovarian failure and hot flashes is hormone replacement therapy. However, estrogen replacement therapy is a concern for some patients due to an associated increase in the risk of breast cancer. Cancer survivors are contraindicated for estrogen replacement therapy [10]. Recent data from the Women's Health Initiative Trial [11], a randomized controlled trial of hormone therapy with estrogen and progestin as primary prevention in post-menopausal women, suggest that women who take hormone therapy long term have a 1.2 to 2.0 fold increased risk of developing breast cancer. In the Women's Health Initiative Trial, the incidence of breast cancer increased by 26% for women in the estrogen-progestin group. In addition, hormone therapy was shown to be associated with increased cardiovascular disease and stroke. Because of these serious concerns many women reject estrogens [12] and health care providers are reluctant to prescribe it. As a result, there is a need for non-pharmacological interventions for women who suffer from hot flashes.

Because of these concerns about hormonal interventions, efforts have been made to identify non-hormonal agents for hot flashes. Studies have been conducted to investigate the use of: soy supplementation [13] vitamin E [14], gabapentin [15], black cohosh and St. John's wort [16] and clonidine [10,17]. Soy does not seem to be much more effective, or only modestly more effective than placebo [4]. None of these agents have been found to be very efficacious and can be associated with a high toxicity profile [4,18,19].

Other studies have investigated the use of antidepressant medication for hot flashes. In a pilot study of breast cancer survivors, the use of paroxetine hydrochloride (Paxil), showed a mean reduction of hot flashes of 67% [4]. However, adverse reactions to the treatment included somnolence and anxiety in 16% of the participants resulting in discontinuation or reduction in medication. A pilot study to investigate the use of venlafaxine hydrochloride for hot flashes in cancer survivors found that the subjects who completed the study reported a 58% reduction in hot flashes [20]. However, negative effects were found in some participants and included symptoms of depression, dry mouth, fatigue, sleepiness, and difficulty with concentration. More recently, prospective randomized clinical trials have confirmed these findings. Venlafaxine reduced hot flashes by 60% compared to a 20% reduction with placebo [21]. Paroxetine reduced hot flashes by 45-65% in post-menopausal women [22,23]. Similar results were observed in breast cancer survivors [23]. Fluoxetine decreased hot flash frequency by 50% compared to 36% in placebo [24]. Other studies suggested that sertraline was no more effective than placebo in decreasing hot flashes [25].

While these agents are non-hormonal and are not thought to increase the risk of breast cancer they do have side effects that may reduce tolerance for some patients. Also, drug interactions can limit their use and they are not effective for all patients, especially women on anti-estrogen treatment. Importantly, non-hormonal agents have only modest activity in the treatment of hot flashes and have not been found to be as effective as hormonal therapy [19]. Given these facts, it is imperative that effective new interventions be developed to help post-menopausal women who experience hot flashes.

Hypnosis has been demonstrated to be a potentially effective treatment for hot flashes in breast cancer survivors. A study was completed to evaluate the effectiveness of hypnosis for reducing hot flashes among 16 breast cancer survivors [26]. In this study, 16 women with a history of hot flashes demonstrated that a hypnosis intervention could achieve approximately 69% reduction in hot flash scores relative to baseline among breast cancer survivors. In this single arm pilot study we investigated the use of hypnosis to reduce hot flashes [27]. Each patient provided baseline data and received weekly sessions of hypnosis that followed a standardized transcript that allowed for individualization of mental imagery for relaxation and coolness. Throughout the clinical care, participants completed daily diaries of the frequency and severity of their hot flashes. The hot flash score, a measure of severity and frequency, was determined by multiplying the daily frequency of hot flashes by their average severity. Results indicated a 58.6% decrease in total daily hot flashes and a 69.8% decrease in weekly hot flash scores from their baselines. Based upon our initial findings we then completed a second study under the auspices of an R-21 grant. In this study breast cancer survivors with hot flashes were randomized to either a therapist delivered hypnosis intervention or a wait-list control condition. Participants in the hypnosis intervention received 5 sessions of individual hypnosis delivered by a trained hypnotherapist and with individualization of mental imagery for coolness [28]. Results demonstrate that by the end of the treatment period, hot flash scores (frequency × average severity) decreased 68% from baseline to endpoint in the hypnosis arm (*p *< .001). Also, significant improvements in self-reported anxiety, depression, interference of hot flashes on daily activities, and sleep were observed for patients who received the hypnosis intervention (*p *< .005) in comparison to the no-treatment control group.

## Methods/design

### Subjects

A total of approximately 180 post-menopausal women will be entered into the study. A screening checklist will be used to determine eligibility. Participants will be randomly assigned to either a hypnosis intervention or structured-attention control.

### Eligibility Criteria

Eligibility criteria were developed in reference to the Department of Health and Human Services, Food and Drug Administration (FDA) draft recommendations [29], research guidelines [30,31]. Postmenopausal as defined by 1) no menstrual period in the past 12 months; 2) no menstrual period in the past 6 months and a medically documented history of FSH level greater than 40; or 3) women who have had a bilateral oophorectomy. If women have had a hysterectomy and still have their ovaries, they must meet the FSH criteria described above. A participant is eligible if they have a self-reported history of a minimum of 7 hot flashes per day or 50 hot flashes per week at baseline, aged over 18 years and ability to give her own consent for participation in the study, and have discontinued other putative therapies for hot flashes for at least one month prior to enrollment (however, because many of the participants seen in our institutions take vitamin preparations, Vitamin E will be allowed). Further, we participants must be able to attend weekly sessions.

### Exclusion Criteria

Participants will be excluded from participation if they are receiving other simultaneous treatment for hot flashes, or using any CAM (Complementary and Alternative Medicine) treatments for vasomotor symptoms. This would include soy products and other phytoestrogens, black cohosh, and any mind-body techniques including meditation and yoga, etc. Further, participants will be excluded if they have any medical or psychiatric condition that in the opinion of the investigator puts the participant at potential risk during the study, are currently using hypnosis for any reason, or have an inability to speak or understand English.

### Randomization

After the 7-day baseline data have been collected, participants may return the completed daily diary, Biolog^® ^3991 monitor, Bahr monitor and cortisol samples. Between week 0 and week 1 visits, the Research Coordinator will contact the Data Coordinator who will provide random assignment for the participant, and this assignment will be placed in a sealed envelope that will not be opened until the visit at week 1. Random assignment will be made sequentially from a confidential computer-generated list of permuted blocks of varying size. The list is generated to provide equal probabilities to the study arms. The study participants will be randomly assigned by the Data Coordinator to either the hypnosis intervention or to a structured-attention control group. An overview of the chronology of the study is provided graphically [Figure 1].

**Figure 1 F1:**
[figure not shown]
**Study Design**.

### Experimental Intervention

Participants assigned to the hypnosis intervention will be scheduled to meet with a hypnosis research therapist for five visits. All visits will follow eight key components of structured attention guidelines as defined in the treatment manual. In addition, participants in the Hypnosis Intervention will receive a hypnotic induction at each session and a CD recording of a hypnotic induction. The hypnotic induction will follow a well-defined standard transcript but will include mental imagery for relaxation and coolness based on preferences of the participant and encouragement to practice hypnosis on a daily basis with and without the recording.

At the first session the hypnosis research therapist will provide the participant with a handout regarding hot flashes with a hypnosis related description. The use of hypnosis will be discussed and the participant will be provided with information regarding hypnosis. Each participant will be provided with a brief discussion regarding myths and misconceptions about hypnosis and the process used in hypnotic induction [31]. The participants will also be asked to rate their level of anxiety at the beginning of the session and after the hypnotic induction. The research therapist will review a checklist, contained in the treatment manual at each treatment session to ensure consistency.

Participants will be scheduled to return on an approximately weekly basis for sessions 2-5. Each session will include a hypnotic induction and during session 3, a handout with step-by-step instructions in self-hypnosis will be presented. The research therapist will ask the participants about their use of self-hypnosis and their preferences of self-hypnosis (i.e., with the self-hypnosis recording or without using the recording). The research therapist will also discuss the frequency and severity of the participants' hot flashes, and inquire about the effectiveness of self-hypnosis in decreasing the frequency and severity of the hot flashes on a daily basis. Participants will be asked to identify specific imagery for relaxation and imagery for coolness in order to individualize the hypnotic induction based upon the participants' preferences [32].

### Control Intervention

The structured-attention control condition is designed to control for attention, monitoring symptoms, and interpersonal exchange that is inherent in therapeutic hypnosis intervention. In designing our structured-attention control condition we followed the recommendations of Jensen and Patterson [33] that has determined the importance of creating control conditions that include minimal-effect interventions and that are well defined. All visits will follow structured attention guidelines as defined in the treatment manual. The structured attention guidelines will follow eight key components developed specifically for this study. This type of approach (with somewhat different key components for pain control) has previously been used in the study of hypnosis with medical participants [34].

Participants assigned to the structured-attention control condition will meet with a research therapist for five individual approximately weekly visits. The eight key components will be: Information (i.e. causes of hot flashes, triggers for hot flashes); monitoring of hot flashes (i.e. "How many hot flashes did you have yesterday?; "How severe were your hot flashes yesterday?"); rating anxiety (i.e. "Please rate how anxious you feel."); attentive listening; interpersonal exchange; discussion of symptoms (i.e. "How have you been feeling during the past week?": "How have you been sleeping?"); encouragement (i.e. "You are doing well."); and avoidance of negative suggestion. Also, at the first session the research therapist will provide the participant with a handout regarding hot flashes without mention of hypnosis. In addition, participants in the structured-attention control condition will be provided with a CD recording that they can listen to at home. The recording will be approximately the same length of time as the hypnosis recording that those in the hypnosis group will receive, however no hypnotic induction will be provided to the Structured-Attention Control. The research therapist will review a checklist at each intervention session to assure consistency contained in the treatment manual.

### Effect Measures

Outcomes will be hot flashes (self-report daily diaries; physiological monitoring; Hot Flash Related Daily Interference Scale), anxiety (State-Trait Anxiety Inventory; Hospital Anxiety and Depression Scale (HADS); anxiety visual analog scale (VAS rating); depression (Center for Epidemiologic Studies Depression Scale), sexual functioning (Sexual Activity Questionnaire), sleep quality (Pittsburgh Sleep Quality Index) and cortisol; moderators will be cognitive expectancies (VAS ratings) and hypnotizability (Stanford Hypnotic Susceptibility Scale-Form C). A figure representing the schedule of collection is provided [Figure 2].

**Figure 2 F2:**
[figure not shown]
**Data Collection Schedule**.

### Hot Flashes via Sternal Skin Conductance Monitoring

Two different sternal skin conductance monitoring systems may be used to objectively measure hot flash frequency. With the Biolog^® ^ambulatory recorder [35], skin conductance levels are monitored using Medi-Trace silver/silver chloride and a 0.5 constant voltage circuit [36]. Electrodes are 1.5 cm in diameter and filled with 0.05 M potassium chloride Velvachol/glycol gel [37]. Electrodes are attached 1.5" below the collarbones and 2" on either side of the sternal mid-line. Participants will be educated on the proper use of the monitor. The Biolog^® ^monitor is a solid-state device containing a microprocessor and 4 megabytes (MB) of memory. The 3991 was designed by the company with input from the study Consultant, [name], to provide (1) a smaller and more lightweight hot flash monitor and (2) capability for storing 24 hours' worth of data.

The Bahr Hot Flash Monitor [38] may be used to measure objective hot flashes in conjunction with the Biolog^® ^monitor. The Bahr monitor attaches to a 1" × 2" cloth patch that contains the two electrodes to be placed in the midline over the sternum, two to three inches below the sternoclavicular notch. Prior to connection with the electrodes, the monitor should be synchronized and time stamped with the Bahr watch and software. The monitor should then be activated using a magnet until the green light flashes. The activation time and the attachment time should be recorded in the Monitor Log. When the participant subjectively observes a hot flash, they will be instructed to pass the magnet close to the monitor and a red light will flash to indicate acceptance of the marker. The monitor will measure skin conductance every ten seconds. The participant may wear the monitor for simultaneous comparison with the Biolog^® ^monitor. One advantage of the Bahr monitor is that the dimensions are much smaller than the Biolog^® ^(6 × 2 × 1 cm) and is light enough to simply hang from the chest leads without carrying an extra bag to store the device.

### Salivary cortisol

Salivary cortisol samples will be collected four times in the same day by participants during the week before the first session (baseline) and after completing approximately five sessions of the hypnosis intervention or structured-attention control. Instructions will be provided to participants upon receipt of the cortisol materials. Pre- and post-session salivary cortisol samples will also be collected at the participants' first session with the research therapist. Salivary cortisol samples will be assayed with a time-resolved immunoassay with a cortisolbiotin conjugate as a tracer. Total cortisol produced over a day will be measured by calculating the area-under-the-curve (AUC). This represents the total volume of cortisol secretion over the day. We will also examine cortisol levels at each time point averaged across the areas under the curve and mean diurnal and nocturnal levels will be compared and the presence of circadian rhythmicity will be evaluated [39].

### Statistical power and Sample size

Power analyses were conducted using the partial eta-squared (η_p_^2^) from the repeated measures ANOVAs run for the pilot study. Analyses were based on a sample size of 180 (90 per arm) with a conservative estimate of 30% drop-out. Further, it is recognized that there is the possibility of a placebo effect not observed in the pilot study due to the provision of an active control group. Placebo effects of as large as a 30% reduction in hot flash frequencies and hot flash severity scores have been reported (Sloan et al., 2001). Thus, the calculations reported here are based on a sample size of 126 with effect sizes 30% smaller than those from the pilot study.

An overall experiment-wise alpha of 0.05 will be used, with a Dunn/Bonferroni correction to adjust the error rate for individual analyses. Twenty-one separate analyses are planned (8 for Aim 1, 8 for Aim 2, 5 for Aim 3). Thus, these sample size calculations are based on α = 0.00238 (0.05/21).

Power calculations were conducted using pilot data, analyzed using repeated measures ANOVAs with one between-subjects and one within-subjects variable. Calculations were conducted using G*Power and focused on the interaction term from these analyses. G*Power takes into account the expected effect size (η_p_^2^, reduced by 30%), alpha (0.00238), desired power (0.90), correlation between pre- and post-test, and sphericity. The sample size needed for 0.90 power based on these calculations (CES-D, η_p_^2 ^= 0.0672, *r *= 0.492, pre-post) was 72 (sample size calculations using other dependent variables were smaller). Given a sample size of 180, with a 30% drop out/missing data rate, power would be 0.99 for this comparison. Thus, this study is adequately powered even if a higher than anticipated drop out rate occurs, or if missing data reduces the *N *for some of the analyses.

Participant demographic characteristics will be analyzed using descriptive statistics, including baseline characteristics, averages, and related confidence intervals. Hot flash scores and frequencies will be plotted over the study period. The hot-flash score, being a measure of severity and frequency, is determined by multiplying the daily frequency of hot flashes by their severity (Perez et al., 2004). Analysis will be completed to fully examine and explore the data and to test the hypotheses.

Primary analyses will be conducted using a mixed model approach, with each dependent variable analyzed separately as a pretest-posttest control group design with one within-subjects variable (pre-post) and one between-subjects variable (experimental-control). Composites will be used for analyses with multiple scales (e.g., a single sleep composite will be used).

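### Single-step Bonferroni over the 21 planned analyses is dominated by Holm's step-down procedure, which keeps the same family-wise 0.05 and never rejects less

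*Protocol article*

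**What the plan says.** In the Protocol article, the section Statistical power and Sample size fixes the error control in three steps.

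- Method: "An overall experiment-wise alpha of 0.05 will be used, with a Dunn/Bonferroni correction to adjust the error rate for individual analyses".
- Family: "Twenty-one separate analyses are planned (8 for Aim 1, 8 for Aim 2, 5 for Aim 3").
- Per-test level: "Thus, these sample size calculations are based on α = 0.00238 (0.05/21").

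The same section describes the power calculation. The effect sizes come from the pilot: "Power analyses were conducted using the partial eta-squared (η_p_^2^) from the repeated measures ANOVAs run for the pilot study". The target is the group-by-time interaction: "Calculations were conducted using G*Power and focused on the interaction term from these analyses". Among the inputs listed are "alpha (0.00238), desired power (0.90), correlation between pre- and post-test, and sphericity". The one worked result is for the depression scale: "CES-D, η_p_^2 ^= 0.0672, *r *= 0.492, pre-post) was 72". The section adds that the other outcomes needed fewer participants, and that power would be 0.99 with 180 randomised and 30% lost.

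The section goes on to treat each dependent variable's separate analysis as primary. Effect Measures begins its list with "Outcomes will be hot flashes (self-report daily diaries; physiological monitoring; Hot Flash Related Daily Interference Scale") and continues through anxiety, depression, sexual function, sleep and cortisol without ranking them.

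**The concern.** Single-step Bonferroni compares every p-value with 0.05/21, whatever the other 20 show. Holm compares the smallest p-value with 0.05/21, the next with 0.05/20, and so on up to 0.05/1, stopping at the first failure. Both hold the family-wise error at 0.05 without any assumption about how the outcomes are correlated. Holm's thresholds are never stricter, so it is uniformly at least as powerful.

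This matters most where many outcomes may move together, as they could for an intervention expected to act on hot flashes, anxiety, mood and sleep. Each rejection relaxes the threshold for the outcomes still to be tested. Under the written rule, an outcome with p = 0.003 is declared non-significant even if the other 20 all have p-values below 0.00238. Under Holm it would then be tested at 0.05. At stake are true findings lost on some of the 21 outcomes, with no added protection against false ones.

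**Working it through.** **Inputs (Protocol article, Statistical power and Sample size).** Family-wise alpha 0.05; 21 analyses; CES-D partial eta-squared 0.0672, consistent with a pilot value of 0.096 reduced by 30% (0.096 × 0.7 = 0.0672); pre-post correlation r = 0.492; 180 randomised and 30% lost, so 180 × 0.7 = 126 analysed; two groups, two time points.

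**1. Per-test alpha.** 0.05/21 = 0.00238, as stated.

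**2. The plan's own power figures.** f² = 0.0672/(1 − 0.0672) = 0.0720. G*Power's default convention for a within-between interaction gives a noncentrality of λ = f² × N × 2/(1 − r), on 1 and N − 2 degrees of freedom.
- N = 72: λ = 0.0720 × 72 × 2/0.508 = 20.4; power at 0.00238 is 0.908. The stated 72 is reproduced.
- N = 126: λ = 35.7; power at 0.00238 is 0.998 (stated: 0.99).

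On these inputs Bonferroni already has power 0.998 for CES-D, so Holm can add at most 0.2 percentage points.

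**3. The same effect if the correlation is already in it.** A partial eta-squared taken from a repeated-measures ANOVA normally reflects the pre-post correlation already. If 0.0672 is such a value, λ = f² × (N − 2) = 0.0720 × 124 = 8.93, and power at 0.00238 with 126 analysed is 0.46 by the noncentral F. In the normal approximation used for the simulation, the mean is √8.93 = 2.99, the two-sided critical value is 3.04, and power is 0.48. The article does not say which G*Power effect-size option was used, so this is an assumption.

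**4. Holm controls the same error.** Let m₀ of the 21 null hypotheses be true. At Holm's first false rejection, at most 21 − m₀ hypotheses have been rejected before it, so the threshold there is at most 0.05/m₀. A false rejection therefore needs at least one true-null p-value at or below 0.05/m₀, which has probability at most m₀ × 0.05/m₀ = 0.05, whatever the correlation. In simulation with no real effects (100,000 runs), the chance of any rejection was 0.049 at correlation 0 and 0.035 at correlation 0.5.

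**5. What Holm adds under the assumption in step 3.** Simulation of 21 z-tests, pairwise correlation 0 and 0.5. The ranges cover both correlations and a mean of 2.99, from f² × (N − 2), or 3.01, from f² × N.

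| Real effects of 21 | Bonferroni, average power per real effect | Holm |
|---|---|---|
| 1 | 0.48–0.49 | 0.48–0.49 |
| 10 | 0.48–0.49 | 0.51–0.52 |
| 16 | 0.48–0.49 | 0.54–0.55 |
| 21 | 0.48–0.49 | 0.58–0.60 |

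The gain runs from none to about 11 percentage points. Every real effect is given the CES-D size here, because it is the only one reported.

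**The case against.** The strongest reply is that nothing is in error. Bonferroni over all 21 analyses is prespecified, valid under any dependence, and was budgeted for: the sample size was computed at 0.00238, and the figures reproduce. On those figures there is almost nothing to gain. All of that stands, and it makes this an efficiency point, not a fault in validity. It does not make Bonferroni the better choice. The 0.998 rests on a convention that may count the correlation twice, and on pilot effects against a wait-list control, whereas this trial has an active attention control. The article itself allows for a placebo response and cuts its effect sizes by 30% for it. If true effects are smaller than planned, Holm can recover power and cannot lose any.

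A second reply is that Holm does little when few outcomes respond, because its first step is still 0.05/21. That is correct, and the table shows it.

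A reader might go further and infer that testing hot flashes at 0.00238 roughly halves the power on the trial's central question. The documents do not support this. The fall from 0.84 at 0.05 to 0.46 at 0.00238 uses the CES-D effect, which the article presents as the outcome needing most participants, and it appears only under the assumption in step 3. On the article's own method the comparison is above 0.999 against 0.998. Nor can a missing ranking of outcomes be held against this article, since the full protocol or the SAP may contain one.

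**Conclusion.** The point holds as a low-cost improvement. The article commits to a single-step procedure that Holm dominates: same family-wise 0.05, same freedom from dependence assumptions, never fewer rejections. That part rests on no assumption about effect sizes.

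The size of the benefit does. It is negligible if the article's power calculation is right, zero to about 11 percentage points of average power per real effect if 0.0672 already includes the pre-post correlation, and largest when many outcomes respond. A power loss specific to hot flashes cannot be stated from this document.

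**What to change.** In Statistical power and Sample size, replace the Dunn/Bonferroni correction with the Holm step-down procedure across the 21 analyses, at a family-wise two-sided 0.05. The calculation at 0.00238 can remain, described as the first-step and therefore conservative level. Make the change before any comparison by arm is seen; the article reports that the trial was still accruing.

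The cost is one change of wording. Simultaneous confidence intervals that match Holm are less simple than Bonferroni intervals. The procedure is also completed only when all 21 p-values are available, although any at or below 0.05/21 can be declared at once.

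An option for the sponsor to consider, not a correction, is a gated order with one hot-flash outcome tested first at 0.05 and Holm applied to the other 20 only if it succeeds. This gives the lead test the full 0.05. If the lead outcome fails, the other 20 become descriptive, and these would include physiologically monitored hot flashes if the diary score were the lead. Which outcome leads is a scientific choice.

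### The CES-D power figures (N = 72, power 0.99) apply the factor 2/(1 − r) to a partial eta-squared that already contains it; on the plan's own inputs they become about 266 and 0.46

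*Protocol article*

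**What the plan says.** All of this is in the protocol article under Statistical power and Sample size.

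- Source of the effect size: "Power analyses were conducted using the partial eta-squared (η_p_^2^) from the repeated measures ANOVAs run for the pilot study". It was then reduced by 30% to allow for a placebo response.
- Test: "Calculations were conducted using G*Power and focused on the interaction term from these analyses". The pilot data were "analyzed using repeated measures ANOVAs with one between-subjects and one within-subjects variable".
- Further software inputs, besides effect size and alpha: "desired power (0.90), correlation between pre- and post-test, and sphericity".
- Alpha: 0.00238, which is 0.05 divided by 21 planned analyses.
- Result for the CES-D (partial eta-squared 0.0672, r = 0.492): the total needed "was 72 (sample size calculations using other dependent variables were smaller").
- Power for the planned trial: "Given a sample size of 180, with a 30% drop out/missing data rate, power would be 0.99 for this comparison". Thirty per cent loss from 180 leaves 126.

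The section concludes that power remains adequate if dropout is higher than expected or if missing data shrink some analyses.

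**The concern.** A partial eta-squared from a repeated measures ANOVA sets the interaction sum of squares against the within-subject error. That error term is already small when the pre-post correlation is high. Entering the correlation again, in a formula that expects an effect size on the raw-score scale, credits the design twice for the same gain.

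The article presents the CES-D as the outcome needing the largest sample, so the adequacy statement for the whole trial rests on this calculation. If the figure is wrong, the trial reports near-certain power for a comparison that has roughly an even chance, and treats further dropout as harmless when it is not.

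**Working it through.** **Inputs**, all from Statistical power and Sample size: partial eta-squared 0.0672; r = 0.492; m = 2 measurements; two equal arms; alpha = 0.05/21 = 0.00238; target power 0.90; 180 randomized, 126 after 30% loss.

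f² = 0.0672/(1 − 0.0672) = 0.0720. The test is a noncentral F with 1 and N − 2 degrees of freedom and noncentrality λ.

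**1. Reproducing the plan's figures.** Take λ = f² × N × m/(1 − r), with m/(1 − r) = 2/0.508 = 3.94.

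- N = 70: λ = 19.85, power 0.897
- N = 72: λ = 20.42, power 0.908
- N = 126: λ = 35.74, power 0.998

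The smallest N is 71, or 72 with equal arms. Both stated figures are recovered. Other forms do not give 72: m alone gives 136, 1/(1 − r) alone gives 138, and neither gives 264 to 266 (equal arms throughout).

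**2. Why the factor does not belong.** Let δ be the difference in mean change and σ the SD at each time point.

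- The change score has variance 2σ²(1 − r).
- In a 2 × 2 pre-post design the interaction F is the squared two-sample t on change scores. So the ANOVA-scale effect is f² = δ²/[4 × 2σ²(1 − r)] = δ²/[8σ²(1 − r)].
- On the raw-score scale the interaction effect is f²(raw) = δ²/(16σ²).
- Hence f²(raw) × 2/(1 − r) = δ²/[8σ²(1 − r)], which is the ANOVA-scale f².

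The factor 2/(1 − r) therefore converts a raw-scale effect to the ANOVA scale. A value taken from the ANOVA is already there. Both parts of the factor, the 2 and the 1/(1 − r), must go. Since partial eta-squared = F/(F + N − 2), the matching noncentrality is λ = f² × (N − 2).

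**3. Corrected figures**

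| Completers | λ = f²(N − 2) | Power |
|---|---|---|
| 72 | 5.04 | 0.19 |
| 126 | 8.93 | 0.46 |
| 180 | 12.82 | 0.69 |
| 266 | 19.02 | 0.90 |

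Using λ = f² × N instead gives N = 264 and power 0.47 at 126. Simulation of the change-score t-test (100,000 runs) gave 0.201 at 72, 0.468 at 126 and 0.902 at 266.

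**4. Sensitivity to the 30% reduction.** The match at 72 requires 0.0672 to be the value after the reduction. If it were the value before, 0.0672 × 0.7 = 0.0470 would apply; N would be about 386 and power at 126 would be 0.27.

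**5. What 126 completers can detect** at 0.90 power: partial eta-squared about 0.135, or about 0.78 SD of the change score (0.784 from the noncentral t with 63 per arm; 0.79 if converted from 0.135).

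**The case against.** **The software option is not stated.** The article does not say which effect-size convention was used, and the unconstrained minimum is 71 and not 72. This stands as a caveat. The equal-arm match at 72, with r listed as an input, makes the inference strong. If 0.0672 were already a raw-scale value, the stated figures would be right; but the text says that it comes from the pilot ANOVA. For the stated figures to hold, the ANOVA-scale f² would have to be 0.0720 × 3.94 = 0.284, a partial eta-squared of about 0.22.

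**It is not only the correlation.** This stands. Removing 1/(1 − r) but keeping m = 2 gives 136 and power 0.87 at 126. An instruction merely not to enter r again would lead to the wrong correction.

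**The CES-D is one outcome among many.** This also stands. The article says that the other outcomes needed fewer participants. With 126 completers, any outcome with a reduced partial eta-squared of about 0.135 or more still has 0.90 power, and about 0.195 gives 0.99. A reader might infer that the trial is underpowered for hot flashes. The document does not support that, because no effect size is given for those outcomes.

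**Physiological hot flashes.** The Abstract says that "the efficacy of hypnosis in reducing physiologically measured hot flashes has not yet been determined". A reader might infer that the pilot took no such measurement, so that no pilot effect size exists. The sentence speaks of efficacy not being established; it does not say what the pilot measured. Only cortisol is described, in the Discussion part of the Abstract, as a first for hypnosis for hot flashes.

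**Conclusion.** The CES-D figures are wrong as written. On the article's own effect size, alpha and completer count, about 266 completers are needed for 0.90 power, against a stated 72. Power at 126 is about 0.46, against a stated 0.99. The statement that the study stays adequately powered under heavier dropout is not supported for this comparison.

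This rests on three assumptions: 0.0672 is an ANOVA-scale value, as the text says; it is the value after the 30% reduction, without which the position is worse; and the software option is the one that reproduces 72. The conclusion extends to no other outcome's power. Those figures need recomputing, but they cannot be recomputed from what is published.

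**What to change.** - Recompute power for every outcome with the option for a partial eta-squared taken from an ANOVA, and name that option in the text.
- For the CES-D, replace 72 with about 266 and 0.99 with about 0.46 at 126 completers.
- Withdraw the sentence on adequacy under higher dropout unless the recomputed figures support it.
- Report the effect detectable with 126 completers at 0.90 power: partial eta-squared about 0.135, or about 0.78 SD of change.
- State that pilot-based power covers only outcomes that the pilot measured, and use the detectable difference for cortisol.

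The cost is one rewritten paragraph, a rerun of the existing calculations, and a less favourable stated power. No extra enrolment is proposed. The article reports that the trial is still accruing, so the correction can be made before results are interpreted.
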